### Intervention group

Participants allocated to the intervention group will receive access to the web-based support programme (https://www.hjartstoppsoverlevare.se) in addition to receiving a printed informational booklet, one-time individual self-management advice and standard post-cardiac arrest care, as defined by current clinical guidelines.^37^, ^38^ The programme is self-guided and designed to be used flexibly, allowing participants to engage with the content according to their individual needs and pace over a 3-months period. Participants are permitted, but not required, to involve a key family member when taking part of the programme.

To promote adherence, participants allocated to the intervention group will receive automated reminders every third week encouraging continued engagement with the digital support programme throughout the access period.

The intervention is grounded in the concept of self-care maintenance, which refers to behaviours aimed at promoting well-being, preserving health, and maintaining physical and emotional stability.^57^ During the intervention, participants are encouraged to set personal goals and create a health plan for their rehabilitation aligned with the programme’s focus areas. Key content is listed in Table 2.

**Table 2 t0010:** Key content in the support programme promoting self-care maintenance.

*Cognitive support*	Information material on common cognitive sequelae (e.g., attention, memory, executive function) and strategies for managing them.
*Emotional support*	Guidance on emotional challenges such as anxiety, depression, post-traumatic stress disorder, fatigue, and sleep disturbances, with suggested exercises in relaxation, breathing, mindfulness, and socialisation.
*Physical rehabilitation*	Education on physical activity and its role in recovery, including practical guidance delivered via video and lectures. The module also highlights the risk of kinesiophobia – fear of movement or physical exertion – which may hinder rehabilitation.
*Lifestyle support*	Guidance on nutrition, alcohol, and nicotine use, with exercises in smoking cessation, alcohol reflection, and healthy eating habits.
*Relationships*	Encouragement to re-establish intimate and social connexions, including exercises to reflect on relationship changes, rebuild social confidence, and explore intimacy with partners.
*Social support*	Encouragement to engage with patient organisations and peer networks, including access to a moderated chat forum via the Swedish network for cardiac arrest survivors and their relatives.
*Personal health planning*	Structured guidance to help participants to reflect on their current situation, identify personal needs and strengths, and formulate meaningful recovery goals. The module is designed to promote autonomy and self-efficacy, and can be completed individually or in collaboration with a family member or healthcare professional.

### Control group

Participants in the control group will receive a printed informational booklet, one-time individual self-management advice, and standard post-cardiac arrest care, as defined by current clinical guidelines.^37^, ^38^ After study completion, participants in the control group will be offered full access to the web-based support programme.

### Harms

Although the intervention is low-risk, participants will be advised to contact the study team if they experience distress or technical issues. Any adverse events or protocol deviations will be recorded and reviewed by the research management team.

### Outcomes and assessments

The primary outcome is overall wellbeing and health between the intervention and control groups 3 months after enrolment.

Secondary outcomes are self-reported HRQoL, life satisfaction, symptoms of depression and anxiety, PTSD, fatigue, cognitive impairment, sleep disturbances, and self-efficacy between the intervention and control groups 3- and 6-months after enrolment.

Assessments will be conducted at baseline, 3 months, and 6 months using self-reported validated digital questionnaires and study specific questions. Data completeness will be automatically monitored, and participants will receive regular reminders to ensure timely data entry. Variables are summarised in Table 3, Table 4.

**Table 3 t0015:** Data collection and assessments.

**Variables**	**Outcome measures**	**Baseline**	**3 months**	**6 months**
***Background variables***				
Sociodemographic variables	Study specific questions	x		
Health literacy	Scale for Communicative and Critical Health Literacy (SCCHL)^60^	x		

***Primary outcome***				
Overall wellbeing and health	Questionnaire on Well-Being (QWB)^58^	x	x	x

***Secondary outcomes***				
Health related quality of life	EuroQol-5D-5L, Visual Analogue Scale^61^	x	x	x
Life Satisfaction	Life Satisfaction Questionnaire (LiSat-11)^62^	x	x	x
Symptoms of anxiety	Generalised Anxiety Disorder Scale (GAD-7)^63^	x	x	x
Symptoms of depression	Patient Health Questionnaire-9 (PHQ-9)^64^	x	x	x
Posttraumatic stress	Impact of Event Scale–Revised (IES-R)^65^	x	x	x
Fatigue	Modified Fatigue Impact Scale (MFIS-21)^66^	x	x	x
Cognition	Cognition (single item question, SIQ)^67^	x	x	x
Sleep	The Minimal Insomnia Symptom Scale (MISS)^68^	x	x	x
Self-Efficacy	General Self-Efficacy Scale (S-GSE)^69^	x	x	x
Healthcare utilisation	Study specific questions		x	x
Return to everyday life	Study specific questions		x	x

**Table 4 t0020:** Sociodemographic variables and study specific questions.

**Variables**	**Measures**	**Baseline**	**3 months**	**6 months**
Sociodemographic	sex, age, origin, residence, occupation, education	x		
Medical history	co-morbidities	x		
Cardiac arrest event	date, location, aetiology	x		
Clinical management care	intensive care, treatment, interventions	x		
Healthcare utilisation	follow-up, acute visits, hospitalisation, encounters, reasons, triggers		x	x
Return to everyday life	return to work/studies, physical activity, fear of recurrence, support		x	x

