**Research questions related to the effect evaluation**
1. What impact does the intervention have on overall wellbeing and health?
2. How does participation affect self-reported HRQoL, cognition, life satisfaction, symptoms of anxiety and depression, PTSD, fatigue, and sleep disturbances?
3. To what extent does self-rated health literacy moderate the effect of the intervention?
4. What influence does the intervention have on general self-efficacy?
5. How does engagement with the intervention and self-management relate to self-reported healthcare utilisation and return to work or studies among individuals of working age?

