### Eligibility criteria

Inclusion: ≥18 years of age, survived cardiac arrest 1–3 months prior to enrolment, access to internet-enabled device.

Exclusion: insufficient linguistic or cognitive ability to engage with the intervention or complete questionnaires designed in Swedish, or concurrent participation in another study collecting patient-reported outcome measures (PROMs) as primary endpoints.

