### Sample size calculation and statistical analysis plan

The trial is planned to include 120 participants. A sample size calculation was conducted for the primary outcome variable (QWB). An a priori sample size calculation was conducted using G*Power for a repeated measures design with two groups and three time points (baseline, 3 months, and 6 months). Assuming a medium effect size (*f* = 0.25), a significance level of 5 % (*α* = 0.05), and a statistical power of 80 % (power = 0.80, corresponding to *β* = 0.20), the analysis showed that a total of 86 participants (43 per group) is sufficient to detect statistically significant differences between groups over time. To account for an estimated attrition rate of 30 %, a total of 120 participants (60 per group) will be recruited.

Baseline characteristics will be compared using chi-square, *t*-tests, or appropriate non-parametric methods. The intervention effect will be evaluated using linear mixed models (LMM) including fixed effects for time, group, and their interaction to assess differential changes over time between groups. Both random intercepts and slopes will be considered to account for individual variability in baseline levels and change over time.

All analyses will follow the intention-to-treat principle, whereby participants are analysed in their originally assigned groups regardless of adherence to the intervention.

There is no formally established minimal clinically important difference (MCID) for the QWB scale. However, previous research has shown that a total score below 50 is associated with clinically significant psychological distress.^58^ Effect sizes will be evaluated using marginal *R*^2^ and conditional *R*^2^.

Secondary outcomes will be analysed exploratorily. Although no formal power calculation has been conducted for these outcomes, their inclusion aims to provide a broader understanding of the potential effects of the intervention.

Adjustments for multiple comparisons, such as Bonferroni corrections, will be considered to control the risk of type I error.

No interim analyses are planned, as there are no anticipated safety concerns and the intervention does not involve clinical risk.

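### Return to everyday life is a secondary outcome without a baseline, so recovery before enrolment dilutes the arm comparison and can confound the engagement question

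*Protocol article*

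**What the plan says.** - **Status and schedule.** Table 3 carries the row "Return to everyday life Study specific questions" under the secondary outcomes, marked at 3 and 6 months with the baseline cell empty. Table 4 gives the content as "return to work/studies, physical activity, fear of recurrence, support", again without a baseline mark. The nine secondary outcomes measured by scales are marked at all three visits.
- **Nearest baseline item.** The sociodemographic row of Table 4 records "sex, age, origin, residence, occupation, education". Nothing shown at baseline corresponds to physical activity, fear of recurrence or support.
- **Time of enrolment.** Under Eligibility criteria, patients must have "survived cardiac arrest 1–3 months prior to enrolment".
- **Text of Outcomes and assessments.** It states: "Secondary outcomes are self-reported HRQoL, life satisfaction, symptoms of depression and anxiety, PTSD, fatigue, cognitive impairment, sleep disturbances, and self-efficacy". Return to everyday life and healthcare utilisation are not in that list. The same section says: "Assessments will be conducted at baseline, 3 months, and 6 months using self-reported validated digital questionnaires and study specific questions".
- **Research question.** Effect question 5 in Table 1 relates engagement and self-management to healthcare use and to "return to work or studies among individuals of working age".
- **Model.** The sample size and analysis section gives one model for the intervention effect, a linear mixed model "including fixed effects for time, group, and their interaction to assess differential changes over time between groups". Secondary outcomes are called exploratory and have no power calculation.

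**The concern.** The clock for recovery starts at the arrest, not at randomisation. By enrolment some patients may already be working, studying or physically active. At month 3 they count as returned, although the programme cannot have caused it. Because the same items are not asked at entry, the data cannot show who was still able to return.

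Three things are at stake. The difference between arms is diluted by people whose outcome was settled before allocation. The precision that a baseline answer would bring to the scaled items is lost. And effect question 5 compares participants by how much they used the programme, which is not randomised: someone already back at work may use it more or less than someone on sick leave, so baseline work status is a plausible confounder that is not shown to be recorded.

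This is a stated schedule, given twice, rather than detail that an article leaves to an analysis plan. No later plan can analyse data that were not collected.

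**Working it through.** **The plan's own figure.** No sample size is given for this outcome. The stated 86 is for the QWB. It is reproduced by the repeated-measures between-groups test with f = 0.25, 3 occasions and correlation 0.5 (my assumption; not stated): noncentrality = 0.25² × 86 × 3 / (1 + 2 × 0.5) = 8.06, power 0.801. After 30% attrition, 120 × 0.70 = 84 remain, or 42 per arm.

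**Dilution of return to work.** Let q be the share already back at enrolment, and p the return rate among the others. The observed proportion is q + (1 − q)p, so the observed difference is (1 − q) times the true one. The documents give neither q nor p; all values here are assumed.

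| q | Control (p = 0.40) | Intervention (p = 0.60) | Observed difference |
|---|---|---|---|
| 0 | 0.40 | 0.60 | 20 points |
| 0.1 | 0.46 | 0.64 | 18 points |
| 0.3 | 0.58 | 0.72 | 14 points |
| 0.5 | 0.70 | 0.80 | 10 points |

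With 40% versus 70% and q = 0, 0.2 and 0.4, the difference is 30, 24 and 18 points. Power for two proportions, Φ[(d − 1.96·SE₀)/SE₁], at 43 per arm is 81%, 64% and 47%. For q = 0.2: proportions 0.52 and 0.76, SE₀ = √(0.64 × 0.36 × 2/43) = 0.1035, SE₁ = √((0.2496 + 0.1824)/43) = 0.1002, so Φ(0.37) = 0.64. Using 43 per arm treats every participant as being of working age, so real power would be lower.

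Restricting to those not yet back restores the full difference on fewer people. At q = 0.2, about 43 × 0.8 = 34 per arm remain, and the same formula with 0.40 and 0.70 gives about 71%. At q = 0.4, about 26 per arm remain, giving about 58%. Part of the loss is recovered, not all of it.

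**Precision for a scaled item.** Assume a 0.5 SD effect at month 3, 42 per arm, and correlation ρ between baseline and month 3.
- Unadjusted: SE = √(2/42) = 0.218; 0.5/0.218 = 2.29; power Φ(2.29 − 1.96) = 63%.
- Baseline-adjusted at ρ = 0.6: SE = 0.218 × √(1 − 0.36) = 0.175; 0.5/0.175 = 2.86; power about 82% by normal approximation. A simulation of 20,000 trials gives 80.2%, and 62.5% unadjusted.
- Over ρ = 0.3, 0.5 and 0.7 at 43 per arm, adjusted power is 68%, 76% and 90%, against 64% unadjusted.

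**The stated model with two visits.** Code month 3 as 0 and month 6 as 1. The group coefficient is then the month-3 difference. The interaction is the month-6 difference minus the month-3 difference. For a benefit of 0.5 SD reached by month 3 and kept, the interaction is 0.5 − 0.5 = 0, and its test rejects at the 5% significance level only. For a benefit growing from 0.25 to 0.5 SD (ρ = 0.5, 43 per arm), SE = √(2 × 0.5) × √(2/43) = 0.216, 0.25/0.216 = 1.16, and power is about 21%. The group coefficient for 0.5 SD has 64%.

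**The case against.** Several stronger readings are tempting, and the documents do not support them.

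- **The model sees only the change from month 3 to month 6.** It does not. It has a group term as well, and with two visits that term estimates the follow-up difference. Nor does the article say that the interaction test will be used for these items: the model is given for the intervention effect, straight after a three-visit calculation for the QWB, and secondary outcomes are dealt with separately as exploratory. The limitation is therefore conditional on someone applying the interaction to two-visit items.
- **The arm comparison is biased.** Allocation is 1:1, stratified by site, and analysis is by assigned group. Early returners are balanced in expectation. The cost is dilution and lost precision.
- **Chance imbalance adds a large hidden error.** With an assumed 21 working-age completers per arm, the SD of the imbalance in the share already back is √(2q(1 − q)/21), or 9, 14 and 15 points at q = 0.1, 0.3 and 0.5. It reaches the outcome only through people who would otherwise not have returned. At 40–60% return, 14 points become about 6 to 8, and that variation is already in the ordinary standard error.
- **Question 5 is a by-arm comparison.** It concerns engagement, so a by-arm analysis does not answer it. What stands there is confounding.

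The questionnaires are also not shown. Baseline occupation might record current working status, or the follow-up item might ask for the date of return. Either would settle the return-to-work part, but not physical activity, fear of recurrence or support. Finally, the text's list omits this outcome, so its secondary status rests on Table 3 alone. The general sentence on assessments could be read as placing study-specific questions at baseline, but Table 4 does have such items at baseline (the sociodemographic ones), so it does not override the empty cells.

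**Conclusion.** The point holds in a limited form. As scheduled in both tables, return to everyday life has no baseline, while enrolment comes late enough for some recovery to have happened. The consequences are a diluted arm comparison for return to work, a loss at month 3 of roughly 17 percentage points of power for a scaled item under the main assumptions (63% against 80%), and an open route to confounding in question 5. The last is the strongest ground for action, because randomisation gives no protection there.

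The shares already back, the return rates, the effect size, the correlation and the scaled format of the items are assumptions. The direction of the dilution does not depend on them; its size does. Because these outcomes are exploratory and unpowered, the severity is modest. The change is still worth making, since it is cheap before main recruitment and cannot be made afterwards.

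**What to change.** 1. In Tables 3 and 4, mark return to everyday life at baseline: working or studying before the arrest, already back and to what extent, physical activity, fear of recurrence, support.
2. Analyse return to work or studies by randomised arm among working-age participants who worked or studied before the arrest and had not returned at baseline. Have the form completed before allocation, so that this subset is defined by pre-randomisation data.
3. For the other items, report the difference between arms at 3 and at 6 months, adjusted for the baseline answer, rather than the interaction of months 3 and 6.
4. Include baseline work status in the analysis of question 5, and describe that analysis as an association.
5. Reconcile the list of secondary outcomes in Outcomes and assessments with Table 3, which also has healthcare utilisation.

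**Cost.** A slightly longer digital baseline questionnaire, an ethics and registry amendment, and a smaller analysis set for return to work. Under Trial status, main recruitment starts in autumn 2026, so if the change is made before then only pilot participants would lack the items.

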#### Process evaluation

Specific attention will be given to evaluate adherence and potential social selection bias.

*Social selectivity* will be collected by keeping logbooks in the screening process in patients who accept vs. decline study participation (age and gender) and calculate the number of patients who do not meet the inclusion criteria for the intervention.

*Adherence to the study* will be monitored by calculating the number of participants who complete the study, discontinue participation, or fail to complete all questionnaires.

*Adherence to the intervention* (number of accesses and total time spent on the digital programme in the intervention group) will be analysed using continuous log-data integrated into the platform.

*Experience of the intervention* will be analysed using study specific questions. These address frequency and mode of programme use (individual vs. together with a key family member), the specific components accessed, and perceived helpfulness for recovery and future outlook.

### Sample size calculation and statistical analysis plan

The trial is planned to include 120 participants. A sample size calculation was conducted for the primary outcome variable (QWB). An a priori sample size calculation was conducted using G*Power for a repeated measures design with two groups and three time points (baseline, 3 months, and 6 months). Assuming a medium effect size (*f* = 0.25), a significance level of 5 % (*α* = 0.05), and a statistical power of 80 % (power = 0.80, corresponding to *β* = 0.20), the analysis showed that a total of 86 participants (43 per group) is sufficient to detect statistically significant differences between groups over time. To account for an estimated attrition rate of 30 %, a total of 120 participants (60 per group) will be recruited.

Baseline characteristics will be compared using chi-square, *t*-tests, or appropriate non-parametric methods. The intervention effect will be evaluated using linear mixed models (LMM) including fixed effects for time, group, and their interaction to assess differential changes over time between groups. Both random intercepts and slopes will be considered to account for individual variability in baseline levels and change over time.

All analyses will follow the intention-to-treat principle, whereby participants are analysed in their originally assigned groups regardless of adherence to the intervention.

There is no formally established minimal clinically important difference (MCID) for the QWB scale. However, previous research has shown that a total score below 50 is associated with clinically significant psychological distress.^58^ Effect sizes will be evaluated using marginal *R*^2^ and conditional *R*^2^.

Secondary outcomes will be analysed exploratorily. Although no formal power calculation has been conducted for these outcomes, their inclusion aims to provide a broader understanding of the potential effects of the intervention.

Adjustments for multiple comparisons, such as Bonferroni corrections, will be considered to control the risk of type I error.

No interim analyses are planned, as there are no anticipated safety concerns and the intervention does not involve clinical risk.

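### The N of 86 matches a test of the group difference averaged over baseline, 3 and 6 months, so 80% power is not established for the 3-month primary outcome or the group-by-time model

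*Protocol article*

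**What the plan says.** Under *Outcomes and assessments*, the protocol article fixes a single time point: "The primary outcome is overall wellbeing and health between the intervention and control groups 3 months after enrolment". The instrument is the QWB.

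Under *Sample size calculation and statistical analysis plan*, the calculation was made "using G*Power for a repeated measures design with two groups and three time points (baseline, 3 months, and 6 months"). The effect input is given as "Assuming a medium effect size (*f* = 0.25"); α is set at 0.05 and the target power at 0.80. The result is that "a total of 86 participants (43 per group) is sufficient to detect statistically significant differences between groups over time". Then: "To account for an estimated attrition rate of 30 %, a total of 120 participants (60 per group) will be recruited".

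The same section specifies a linear mixed model with "fixed effects for time, group, and their interaction to assess differential changes over time between groups".

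The section does not name the G*Power test option, the correlation among repeated measurements, or a QWB difference and SD. It notes that no minimal clinically important difference is established for the QWB.

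**The concern.** Three statements should refer to the same comparison: the primary outcome (3 months), the model (group by time) and the power calculation. The number 86 points to a different comparison, the group difference averaged over all three visits. One of those visits precedes treatment, and there randomisation makes the expected difference zero. Including it dilutes the averaged effect.

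This is the only power statement in the article, and there is no established clinically important difference to read a result against. Readers of a null result will therefore rely on the claim of 80% power for a medium effect. If that figure belongs to another test, a null result may be given more weight than it deserves.

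**Working it through.** **Inputs from the article:** f = 0.25, α = 0.05, power 0.80, 2 groups, m = 3 measurements, 1:1 allocation, N = 86, 120 recruited, 30% attrition.

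**Assumptions (not in the article):** correlation ρ = 0.5, varied from 0.3 to 0.7; equal variances and a common correlation across visits; F tests, equivalent to two-sided t tests when the numerator has 1 df. For two groups, f = 0.25 corresponds to a difference of 2 × 0.25 = 0.5 SD.

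**Step 1. Reproduce 86.** For G*Power's between-factors test, λ = f²·N·m / (1 + (m−1)ρ), with df 1 and N−2.
- N = 86, ρ = 0.5: λ = 0.0625 × 86 × 3 / 2 = 8.06, power 0.801.
- N = 84: power 0.792. So 86 is the smallest even N that reaches 80%.
- At ρ = 0.3, 0.6 and 0.7 the same option needs 70, 96 and 104.

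**Step 2. Try the interaction options.**
- Default within-between interaction, λ = f²·N·m / (1−ρ): N = 28 at ρ = 0.5, and 38 to 18 for ρ from 0.3 to 0.7.
- SPSS-type effect-size definition: N = 82 at ε = 1, and 86 only with ε near 0.92.

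The between-factors option gives 86 with ρ = 0.5 and no other special setting, so it is the likeliest source.

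**Step 3. What an averaged 0.5 SD means here.** With a baseline difference of 0 and an equal difference d at 3 and 6 months, the average is (0 + d + d)/3 = 2d/3. Setting 2d/3 = 0.5 gives d = 0.75 SD at both follow-up visits, which is more than the medium effect that the article names.

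**Step 4. Power with differences of 0, 0.5 and 0.5 SD, N = 86, ρ = 0.5.**
- *Group effect averaged over visits:* average difference 0.333 SD, so f = 0.1667 and λ = 0.1667² × 86 × 3 / 2 = 3.58; power 46%.
- *Change from baseline to 3 months (the model's 3-month group-by-time contrast):* variance factor 2(1−ρ) = 1, λ = (86/4) × 0.25 / 1 = 5.375; power 63%.
- *Baseline-adjusted 3-month contrast:* variance factor 1−ρ² = 0.75, λ = (86/4) × 0.25 / 0.75 = 7.17 on 1 df; power 75%.
- *2-df group-by-time test:* the squared deviations of (0, 0.5, 0.5) from their mean sum to 0.1667, λ = (86/4) × 0.1667 / 0.5 = 7.17 on 2 df; power 66%.

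**Step 5. Sensitivity to ρ (N = 86, 0.5 SD).**

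| Test | ρ = 0.3 | ρ = 0.5 | ρ = 0.7 |
|---|---|---|---|
| 3-month change contrast | 49% | 63% | 84% |
| Baseline-adjusted, 3 months | 67% | 75% | 89% |
| 2-df interaction | 51% | 66% | 88% |

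The baseline-adjusted contrast passes 80% at ρ of about 0.58.

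**Step 6. Sensitivity to retention (0.5 SD, ρ = 0.5).**
- 120 × 0.70 = 84 completers: change 62%, baseline-adjusted 74% (66–89% for ρ from 0.3 to 0.7). The difference detectable with 80% power is 0.62 SD and 0.54 SD respectively.
- 120 × 0.85 = 102 completers: change 71%, baseline-adjusted 82%.

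**The case against.** **The test option is inferred.** The article does not name it, and an SPSS-type interaction setting with ε near 0.92 also gives 86. This stands: the interaction cannot be ruled out as the source. It would, however, require a non-default ε that the article does not mention.

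**A reader might infer that the calculation assumes the arms already differ by 0.5 SD at baseline.** It does not. The between-factors f fixes only the averaged difference, and 0, 0.75 and 0.75 SD fits the same input with arms equal at baseline. Under that pattern, with N = 86 and ρ = 0.5, power is 93% for the change contrast, 98% baseline-adjusted and 95.5% for the 2-df interaction. The shortfall thus depends on reading the medium effect as 0.5 SD at follow-up. That reading is reasonable, but it is an assumption, because the article gives no QWB difference or SD.

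**A reader might also infer that 80% power for the primary outcome does not exist.** The article does not support that either. Power depends on an unstated correlation, and at ρ = 0.7 all three relevant tests exceed 80% for 0.5 SD. A higher correlation does not rescue the printed calculation, though, since the between-factors test would then have needed 96 or 104.

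**Taking f = 0.25 literally as the default interaction effect** gives power above 99.9% at N = 86 and ρ = 0.5. But that reading yields N = 28, not 86, and for equal differences at 3 and 6 months it implies about 1.06 SD.

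**84 completers may be pessimistic for month 3.** The 30% attrition is not tied to that visit, the mixed model can use partial data, and *Trial status* sets outcome completeness of at least 85% as a progression criterion. This stands, and it is why results for 102 completers are shown. Even then, the change contrast has 71% power at ρ = 0.5.

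**A condensed article may leave the option and correlation to the full protocol.** That is so, and their absence alone is not the point. The point is that the printed number matches a comparison other than the printed outcome and model.

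**Conclusion.** The concern holds in a limited form. The figure of 86 very probably comes from a test of the visit-averaged group difference, which is neither the 3-month primary contrast nor the group-by-time interaction. The stated 80% power is therefore not established for either. For 0.5 SD at 3 and 6 months, correlation 0.5 and 86 completers, the relevant tests have 63% to 75% power. The result rests on the inferred G*Power option, on 0.5 SD as the meaning of a medium effect at follow-up, and on an assumed correlation; a correlation near 0.6 or higher, or better 3-month retention, would bring the baseline-adjusted contrast to 80%. No estimate, allocation or type I error rate is affected. The error lies in what the power statement claims.

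**What to change.** Redo the calculation for the 3-month group contrast and restate it, naming the contrast (baseline-adjusted, or change from baseline), the difference in SD units, the assumed baseline-to-3-month correlation and the assumed 3-month retention. Possible wording:

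> With 84 of 120 participants contributing at 3 months and a baseline-to-3-month correlation of 0.5, the baseline-adjusted comparison has about 74% power for a QWB difference of 0.5 SD (66–89% for correlations of 0.3 to 0.7). Power of 80% is reached at about 0.54 SD. With 102 participants contributing (85%), power for 0.5 SD is about 82%.

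The assumed correlation should be supported by QWB data or presented as a range. The model text should identify the 3-month contrast as the primary test, so that it matches the restated calculation.

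Enrolment need not change. The cost is a reworded sample-size paragraph, a matching registry text where it carries the same statement, and a less favourable stated power. *Trial status* places the start of main recruitment in autumn 2026, so the correction can be made before then.

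### The mixed model estimates a separate baseline mean in each arm, so its 3-month effect is essentially a difference in change and is less precise than a baseline-constrained or baseline-adjusted estimate

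*Protocol article*

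**What the plan says.** Under Outcomes and assessments the article states: "The primary outcome is overall wellbeing and health between the intervention and control groups 3 months after enrolment". Table 3 names the instrument as the QWB and marks it at all three visits, and the text agrees: "Assessments will be conducted at baseline, 3 months, and 6 months using self-reported validated digital questionnaires and study specific questions".

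The section Sample size calculation and statistical analysis plan bases the sample size on a "repeated measures design with two groups and three time points (baseline, 3 months, and 6 months") and specifies the model: "The intervention effect will be evaluated using linear mixed models (LMM) including fixed effects for time, group, and their interaction". The stated purpose of these terms is to see whether the arms change differently over time. On random effects it adds: "Both random intercepts and slopes will be considered to account for individual variability in baseline levels and change over time". Baseline is therefore modelled as an outcome, with a group main effect alongside it. Nowhere does the article adjust for baseline QWB or require the arms to share a baseline mean. Baseline characteristics are only compared by tests.

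**The concern.** Allocation is randomised 1:1, so the arms have the same expected QWB at baseline. A model with a group main effect still estimates a baseline difference and, through the interaction, subtracts it from the 3-month difference. That adds noise, because the quantity estimated is known to be zero in expectation. The estimate then moves against any chance imbalance: the arm that happens to start higher appears to gain less.

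What is at stake is precision, and so power, for the primary 3-month comparison in a trial of 120 with 30% attrition expected. The same holds for the nine secondary scales that Table 3 marks at baseline.

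**Working it through.** **Inputs from the article.** "Assuming a medium effect size (*f* = 0.25), a significance level of 5 % (*α* = 0.05), and a statistical power of 80" %; 86 evaluable; 30% attrition; 120 recruited (60 per arm).

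**Inputs assumed.** The correlation ρ between repeated QWB scores is not given; 0.3 to 0.7 is shown. Compound symmetry. A 3-month effect of d = 0.5 SD, the two-group equivalent of f = 0.25 (d = 2f). Those lost contribute baseline only, leaving 120 × 0.70 = 84 with follow-up (42 per arm).

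**Step 1: the plan's own figure.** For the between-groups repeated-measures test with m = 3 visits, λ = f²Nm/(1 + (m − 1)ρ). With ρ = 0.5 and N = 86, λ = 0.0625 × 86 × 3 / 2 = 8.06 on 1 and 84 df, and power is 0.801. So 86 reproduces at ρ = 0.5. This makes 0.5 a natural middle value, but it is not evidence about QWB. Attrition: 86/0.70 = 123, close to the stated 120.

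**Step 2: what the planned interaction estimates.** With categorical time and complete data, the group-by-3-month coefficient equals the difference in mean change from baseline. In 120 simulated trials (60 per arm, ρ = 0.5) the two agreed to within 4e-15. With 15% missing at 3 months and 30% at 6 months they stayed close (SD 0.191 against 0.197).

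**Step 3: complete cases.** Per-person variance in σ² units is 2(1 − ρ) for change and 1 − ρ² with baseline adjusted. The ratio is (1 − ρ²)/(2(1 − ρ)) = (1 + ρ)/2, that is 0.65, 0.75 and 0.85 at ρ = 0.3, 0.5 and 0.7. A simulation of 20,000 trials at ρ = 0.5 gave a ratio of 0.754. The correlation of the estimate with the chance baseline difference was −0.50 for change and 0.00 with baseline adjusted.

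**Step 4: the planned intention-to-treat model.** Here the baselines of those lost also enter. Per arm, with 42 followed and 60 enrolled:

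- separate baseline means: (1 − ρ²)/42 + (1 − ρ)²/60
- common baseline mean: (1 − ρ²)/42

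The variance of the contrast is twice each. At ρ = 0.5: 0.75/42 = 0.01786 and 0.25/60 = 0.00417, so the variances are 2 × 0.02202 and 2 × 0.01786, and the ratio is 0.81. A direct generalised least squares calculation with all three visits gives the same standard errors. Power is from the noncentral t with 82 df, two-sided 5%.

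| ρ | SE, separate | SE, common | Variance ratio | Power, separate | Power, common |
|---|---|---|---|---|---|
| 0.3 | 0.244 | 0.208 | 0.73 | 53% | 66% |
| 0.5 | 0.210 | 0.189 | 0.81 | 65% | 74% |
| 0.7 | 0.165 | 0.156 | 0.89 | 85% | 89% |

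At ρ = 0.5 the gain is worth 1/0.81 = 1.23, or about 23% more participants. With the 84 complete cases alone the corresponding powers are 48% to 66%, 62% to 74% and 83% to 89%. Those gains are larger, but they do not describe the planned analysis.

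**The case against.** Time, group and their interaction is a standard longitudinal model. Under randomisation its estimate is unbiased and its type I error is valid, and nothing in the article is false or contradictory here. The article is condensed: it does not say whether time is categorical, which contrast will be reported or what covariance will be used, and an analysis plan may settle these. All of that stands, and it limits the point to efficiency. It does not remove it, because the article names the group main effect and describes the aim as differential change. If time were linear, the interaction would be a slope contrast, still based on change. If group plus interaction were reported, it would with complete data be the raw 3-month difference, again not adjusted for baseline.

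A reader might infer more than the documents support:

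- *That baseline QWB is wasted.* In complete cases, change is no better than follow-up scores alone only when 2(1 − ρ) ≥ 1, so at ρ ≤ 0.5. With the baselines of those lost included, the break-even is where (1 − ρ)²/60 = ρ²/42, about ρ = 0.46. Above that the planned model does gain from baseline, and the article gives no ρ.
- *That chance imbalance is a separate harm or a bias.* It is the same loss of precision seen from another side.
- *That the trial already misses its power target.* That is a separate sample-size question and depends on ρ; at 0.7 the planned contrast has about 85%.
- *That the gain equals one third more participants.* That is the complete-case figure at ρ = 0.5; the planned model gives about 23%.
- *That the change has no downside.* Recruitment and consent places consent before data collection, but no text shown places the baseline questionnaire before randomisation, and the flowchart is not reproduced. Participants are not blinded, so if they knew their arm when answering, assuming equal baseline means could introduce bias.

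**Conclusion.** The point holds as a loss of precision, not as an error of validity. As written, the model frees the baseline means, and its 3-month interaction is essentially a change-from-baseline contrast. Sharing or adjusting for baseline would cut the variance of the primary contrast by about 27%, 19% and 11% at ρ = 0.3, 0.5 and 0.7, which is 13, 9 and 4 percentage points of power. These sizes rest on compound symmetry, a 0.5 SD effect, 30% contributing baseline only, and a correlation the article does not state. The gain shrinks as ρ rises, and random slopes, which the article says will be considered, would change the figures. In theory the constrained estimate is never less precise, so the change is worth making once the timing of the baseline questionnaire is confirmed.

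**What to change.** State in the analysis plan that time is categorical and that the model has time plus group-by-time terms at 3 and 6 months, with no group term at baseline. Alternatively, model 3- and 6-month QWB with baseline QWB, by visit, as a covariate. With missing data the two are close but not identical, so choose one in advance. Name the 3-month contrast as the primary estimate. Treat the secondary scales measured at baseline in the same way.

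Before adopting this, the sponsor should confirm that baseline questionnaires are completed before allocation is known.

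The cost is a sentence of wording and a line of model code, with no extra data or participants. The article places the start of main recruitment in autumn 2026, so this can be settled before the main trial's outcome data exist.
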